#### 2.1.1. Selection Process and School Characteristics

A roster of the primary schools in the city of Cáceres will be drawn up. This list will be categorised according to the nature (public or private) of the potential participating schools, resulting in 26 schools. Subsequently, an explanatory letter with the project’s objectives will be sent to the principals, who will be asked to reply to the e-mail if they decide to participate to receive a more detailed explanation of the project. Schools will have a maximum of 15 days to confirm their participation. As the project will be conducted in PE lessons, the PE teachers must support the principals.

#### 2.1.2. Teachers’ Training Program

PE teachers from participating schools will be involved in a training programme on motivational strategies. The research team will contact teachers who decide to participate in the project by e-mail or mobile phone. This contact aims to guarantee their participation in the project and present the objectives and characteristics of the intervention programme. Teachers who join the PE staff after the intervention programme should establish contact to ensure the full development of the programme. The research team will provide each teacher with a document about the objectives to be achieved in the project and the methodology to be implemented.

Regarding the training programme, at least two sessions will be held in February with the teachers whose schools were designated as the experimental school, each lasting 4 h. In the first session, the explanation and timing of the project and its theoretical basis will be presented. Firstly, the research team will explain the fundamentals of SDT applied to PE, underscoring the promotion of PA practice based on supporting the BPNs. Secondly, the teachers will be divided into work groups for a brainstorming session to co-create different intervention strategies where this theoretical basis can be put into practice to promote autonomy, competence, and relatedness towards PA. These strategies will be shared with the rest of the teachers and supervised by the research team. During the second training session, the research team and the teachers will discuss these strategies’ feasibility and functionality to promote PA both in educational and extracurricular contexts. In other words, the ideas developed in the brainstorming session can be adapted correctly and appropriately to the schools’ educational reality. In addition, the research team will arrange weekly meetings with the teachers to obtain feedback on the strategies developed.

#### 2.1.3. Students’ Characteristics

All 4th- and 5th-graders from the participating schools will be invited to be involved. The parents’ or legal guardians’ consent and the students’ agreement will be required to participate in the study. Finally, the inclusion criteria for participation in the intervention programme will be: (i) to have the families’ or legal guardians’ and students’ consent to participate; (ii) to complete the questionnaires of the study variables; and (iii) not to participate in another programme with similar characteristics during the intervention. The selection of these ages is based on the fact that studies confirm that the adolescent stage is when a number of sport dropout behaviours occur and there are higher rates of inactivity [38,39]. Hence the importance of generating good habits from an early age.

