## 2. Methods

### 2.1. Design and Participants

This quasi-experimental study will be carried out in Cáceres (Extremadura, Spain). Convenience sampling will be conducted in six different Primary Schools. Three schools will be randomly assigned to the control school and the other three schools to the experimental school. The sample size will be estimated using the following formula: *n* = (Z)^2^ (*p*(1 − *p*) e^2^), where “*n*” is the sample size, Z = 1.96 (95% confidence interval), *p* = number of 4th and 5th primary school students in the city where the study will be conducted (±3350 students), and e = margin of error (3%). The minimum sample size (considering a 10% non-response) will be 345 students. All the schools will have similar socio-demographic and built-environment characteristics [37]. School courses in Extremadura run from early September to mid-June, with a Christmas break from late December to early January and a break around March or April for the Easter holidays. As seen in Figure 1, assessments will be completed at baseline at the beginning of the school course (Term 1, February) and after the intervention (Term 2, June). A follow-up measurement will be conducted at the beginning of the following school course (Term 3, October). The study has been agreed upon by the Ethics Committee of the University of Extremadura (120/2018) and follows the guidelines of the Declaration of Helsinki.

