### 2.2. Intervention Based on SDT in Primary School

In February, an informative document will also be given to the families or legal guardians, accompanied by the informed consent to be signed. The research team will go to the schools to collect the data on certain days according to the organisational availability of the teachers during lessons. There will always be at least one research team member in the classroom while the students complete the questionnaires to solve any possible doubts. The questionnaires will be completed on paper in approximately 40 min. The variables described in Section 2.3 will be measured three times: (i) before the intervention (February); (ii) after the intervention (June); and (iii) a follow-up measure at the beginning of the following school year under the same conditions as in the two previous measures (October).

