Given that there is no set duration as the benchmark for an intervention programme to be effective, it was decided to set a duration that was in line with previous programmes carried out in primary education [36,40,41,42]. The intervention programme for promoting motivation and PA in primary schools will be carried out over approximately 4 months (March to June). During this period, the strategies that were co-created jointly with the PE teachers in the schools that form part of the experimental group will be developed. Approximately 10 strategies are expected to be developed to involve different agents (teachers, families, and peers) both in the school and in the out-of-school context. For instance, some possible strategies are introducing new physical-sports activities or sports modalities during free time, sharing the PA carried out outside the school context with the class, involving the families, organising complementary and extracurricular activities that encourage the practice of PA, etc. In this sense, each strategy will be associated with promoting a specific BPN, assuming that each one can favour at least one BPN. The reason for designing these strategies is to ensure that the students acquire a level of autonomy that determines when, how and why to do PA and adequate competence to manage the surrounding environment, face new challenges and acquire specific skills. Moreover, this sporting practice can be performed in the company of friends and family to generate a broader social bond, using PA as a nexus of union between people who intend to practice physical sports activities with other people for greater enjoyment. Each experimental school will carry out the same strategies. However, each teacher will be able to apply them as they see fit, adapting them to their own educational reality, under the supervision of a member of the research team (see Figure 2).

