### 2.3. Measures

The following measures were applied to evaluate the variables at three different times (February, June, and October) in the study participants to determine and identify which students could be part of the intervention programme based on psychosocial and physiological dimensions. To summarise, all the instruments are shown in Table 1.

*Socio-economic Status.* The FAS Scale [46] is an index composed of four items that are indicators of material wealth: How many cars or vans does your family own (0, 1, 2 or more)? Do you have a room to yourself (0, 1)? During the last 12 months, how many times did you go on holiday with your family (0, 1, 2, 3 or more)? How many computers does your family own (0, 1, 2, 3 or more)? The items are scored from 0 to 10. The higher the score, the higher the family’s socioeconomic status. 

*Height and Weight.* Students’ height and weight will be assessed by trained research staff of the same sex as the student. Weight will be measured with a digital electronic scale (model SECA 877), and height will be assessed with a telescopic height-measuring instrument. Both measurements will be taken twice, and the mean value will be used to calculate the body mass index.

*Perceived Need Support in PA.* The Spanish translation of the Perceived Autonomy Support Scale for Exercise Settings [19], adapted by Moreno-Murcia et al. [47], will be used. This scale has 12 items (i.e., “I feel that the PE teacher gives me choices and opportunities about whether to do sport and/or vigorous exercise in my free time”) grouped into a single factor (teacher autonomy support). The response format is a Likert scale ranging from 1 (strongly disagree) to 7 (strongly agree).

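### Eligibility depends partly on what children do after schools are allocated: criterion (iii) by its own terms, criterion (ii) because it has no time point

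*Protocol article*

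**What the plan says.** Section 2.1.3 invites every pupil in grades 4 and 5 of the participating schools. It then lists three inclusion criteria, worded as conditions for taking part in the intervention programme. The first is consent. The other two are "ii) to complete the questionnaires of the study variables; and (iii) not to participate in another programme with similar characteristics during the intervention".

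On timing, section 2.2 states that "The variables described in Section 2.3 will be measured three times": in February, June and October. The same section puts the programme in March to June. Allocation is by school (section 2.1): "Three schools will be randomly assigned to the control school and the other three schools to the experimental school". Section 2.1.2 shows that arms are known in February, because "at least two sessions will be held in February with the teachers whose schools were designated as the experimental school". Consent forms and the baseline questionnaires are also dated February.

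Section 2.3, after naming the same three months, says the measures were applied "to determine and identify which students could be part of the intervention programme based on psychosocial and physiological dimensions".

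Section 2.4 makes change in motivation the primary outcome. It names repeated-measures ANOVA or nonparametric alternatives, plus Bonferroni-corrected paired t-tests.

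**The concern.** An inclusion criterion should be settled before allocation can influence it. A criterion about behaviour while the programme runs is not. The programme's example strategies include new sports in free time, family involvement and organised extracurricular activity (section 2.2). Enrolment in a similar outside programme could therefore plausibly rise or fall in the experimental schools, while control families may look elsewhere. If such children are excluded, the arms no longer hold the groups that allocation created, and the excluded children may differ in kind as well as in number.

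The questionnaire criterion raises the same issue if it reaches beyond February. Completing later questionnaires reflects attendance and engagement, and the primary outcome comes from those same questionnaires. Using the criterion as a filter would also discard children who have some usable follow-up.

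**Working it through.** **Timing of each condition, from the documents**

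- Arms designated: by the February teacher training (section 2.1.2).
- Consent and first questionnaires: February (section 2.2). The order of baseline and disclosure of arms within February is not stated.
- Programme: March to June (section 2.2).
- Criterion (iii): refers to the period of the intervention, so compliance is known only in June. It falls after allocation on any reading.
- Criterion (ii): no time point. February is a possible reading; all three waves is another.
- Section 2.3 clause: ties programme membership to February, June and October. June is the end of the programme and October is after it, so neither can decide who enters. The clause cannot work as written.

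**The plan's own figure.** The only sample figure is 345, said to allow for 10% non-response (section 2.1). As printed, with p = 3350, the formula gives 1.96² × 3350 × (1 − 3350) × 0.03² ≈ −38,790, so 345 is not reproduced. That is a separate matter. Below, 345 serves only as a base for illustration.

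**Illustration 1: what an all-waves reading of (ii) would discard.** Assume all 345 complete February and each completes June and October independently with probability r (assumed). Both later waves complete: r². Exactly one complete: 2r(1 − r).

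- r = 0.95: 0.9025 × 345 = 311 complete; 2 × 0.95 × 0.05 × 345 = 33 have one follow-up.
- r = 0.90: 0.81 × 345 = 279 complete; 2 × 0.90 × 0.10 × 345 = 62 have one follow-up.
- r = 0.80: 0.64 × 345 = 221 complete; 2 × 0.80 × 0.20 × 345 = 110 have one follow-up.

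The second figure in each line is the number of children with a usable follow-up whom an all-waves rule would drop. If February completion also varies at the same rate, the share complete is r³: 0.857, 0.729 and 0.512, or about 296, 252 and 177 of 345.

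**Illustration 2: bias from unequal exclusion, simple mixture.** Let excluded children differ from the rest by d in mean change, and let the excluded shares be q₁ and q₀. The contrast shifts by d × (q₁ − q₀). With d = 0.5 SD and shares of 20% and 10% (all assumed), the shift is 0.5 × 0.10 = 0.05 SD in absolute size. Its direction depends on which arm loses more and whether those lost do better or worse.

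**Illustration 3: bias when retention is correlated with outcome.** With no true effect, correlation ρ between retention and outcome, and a share k retained, the mean of those retained shifts by ρ × φ(z₁₋ₖ)/k, in SD units.

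- k = 0.95: 0.022 at ρ = 0.2; 0.054 at ρ = 0.5.
- k = 0.80: 0.070 and 0.175.
- k = 0.70: 0.099 and 0.248.

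Difference between arms, 95% v 80%: 0.05 to 0.12 SD. For 95% v 70%: 0.08 to 0.19 SD. If both arms keep the same share with the same ρ, the difference is zero.

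**The case against.** The strongest reply is that these are conditions for entering a programme that begins in March, so the questionnaire criterion is most naturally met in February. That is a fair reading. It leaves criterion (ii) as an unstated time point rather than a demonstrated rule to drop non-completers. It does not rescue criterion (iii), which names the intervention period.

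Several stronger conclusions are tempting but unsupported:

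- A reader might infer that the plan removes children from the analysis. It never says so. Analysis sets and missing-data rules may sit in a fuller document that is not shown.
- A reader might infer that any child missing one wave will be dropped. Section 2.4 does not state this. Conventional repeated-measures ANOVA does use complete cases, but a paired test of February against June does not need October.
- A reader might take section 2.3 to mean that pupils are selected on their scores. No psychosocial or physiological threshold appears anywhere. Inviting everyone and then applying criteria is not in itself a contradiction.
- A reader might equate criterion (iii) with a ban on ordinary sport. It concerns similar programmes only, and the trial's own extracurricular activities are not another programme. That the intervention changes uptake of rival programmes is plausible, not shown.

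The illustrations also need restraint. The 10% in section 2.1 is one overall allowance, not a rate per wave. A child absent in June has no June outcome whatever the criterion says, so much of the completion-related bias is ordinary missing data. A child excluded for joining another programme may be fully observed, and there the loss is due to the criterion itself.

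**Conclusion.** The point holds in a limited form. Criterion (iii) conditions eligibility on conduct after allocation. Criterion (ii) lacks a time point, and the section 2.3 clause pulls it towards all three waves in a way that cannot operate. If applied as written, the criteria permit exclusions that may differ by arm, and complete-case methods would add further loss.

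The mechanism follows from the dates in the article. That the programme influences these conditions is an inference from its content. The size is unknown: the 0.05 to 0.19 SD range rests entirely on assumed exclusion shares, correlations and differences in change, and it falls to zero if exclusions are alike in both arms. This should be corrected because the correction is cheap; the documents do not show that the result will be materially biased.

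**What to change.** - Restrict criteria (ii) and (iii) to status at baseline: consent given, baseline questionnaire completed, not currently enrolled in a similar programme.
- State that they apply identically in experimental and control schools. The present wording refers only to participation in the programme. Where possible, settle eligibility before arms are disclosed, since a baseline criterion can still be influenced if February enrolment follows disclosure.
- Analyse every eligible child in the arm of the allocated school, using all available waves in a likelihood-based mixed model that accounts for school. This is valid under missing at random; it does not remove bias if loss depends on unobserved outcomes.
- Record later participation in other programmes as follow-up data and use it only in a sensitivity analysis.
- Delete the section 2.3 clause about identifying which students could be part of the programme.

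The cost is revised wording and slightly more analysis work. Essentially no new data are needed, because criterion (iii) already requires knowing about other programmes. The drawback is possible dilution of the contrast by children who join other programmes, which the sensitivity analysis can describe.

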### 2.2. Intervention Based on SDT in Primary School

In February, an informative document will also be given to the families or legal guardians, accompanied by the informed consent to be signed. The research team will go to the schools to collect the data on certain days according to the organisational availability of the teachers during lessons. There will always be at least one research team member in the classroom while the students complete the questionnaires to solve any possible doubts. The questionnaires will be completed on paper in approximately 40 min. The variables described in Section 2.3 will be measured three times: (i) before the intervention (February); (ii) after the intervention (June); and (iii) a follow-up measure at the beginning of the following school year under the same conditions as in the two previous measures (October).

Given that there is no set duration as the benchmark for an intervention programme to be effective, it was decided to set a duration that was in line with previous programmes carried out in primary education [36,40,41,42]. The intervention programme for promoting motivation and PA in primary schools will be carried out over approximately 4 months (March to June). During this period, the strategies that were co-created jointly with the PE teachers in the schools that form part of the experimental group will be developed. Approximately 10 strategies are expected to be developed to involve different agents (teachers, families, and peers) both in the school and in the out-of-school context. For instance, some possible strategies are introducing new physical-sports activities or sports modalities during free time, sharing the PA carried out outside the school context with the class, involving the families, organising complementary and extracurricular activities that encourage the practice of PA, etc. In this sense, each strategy will be associated with promoting a specific BPN, assuming that each one can favour at least one BPN. The reason for designing these strategies is to ensure that the students acquire a level of autonomy that determines when, how and why to do PA and adequate competence to manage the surrounding environment, face new challenges and acquire specific skills. Moreover, this sporting practice can be performed in the company of friends and family to generate a broader social bond, using PA as a nexus of union between people who intend to practice physical sports activities with other people for greater enjoyment. Each experimental school will carry out the same strategies. However, each teacher will be able to apply them as they see fit, adapting them to their own educational reality, under the supervision of a member of the research team (see Figure 2).

In this regard, we highlight the role of the facilitator within the research team. The supervisor or facilitator role has been used in many contexts to encourage the development of behaviours that significantly benefit individuals [43,44,45]. For a better understanding, the definition established by the Royal Spanish Academy of the facilitator is: “A person who acts as an instructor or guide in an activity”. Facilitators will fulfil various functions to ensure the compliance and correct development of the programme, as well as to assist when necessary in carrying out strategies that are not adequately developed and/or are difficult to implement in that educational context. The main functions of the facilitators will be: (a) to support the teaching team in explaining and developing the strategies in the educational context; (b) to provide all the (physical) material to the different educational centres participating in the study; (c) to carry out weekly monitoring of the fulfilment of the strategies by the teachers; (d) to design a programme of physical-sports activities that include different games and/or sports modalities for break time; and (e) to design a programme of activities for complementary and extracurricular activities to be carried out during the project.

According to objective (c), this monitoring will be carried out through checklists in which items related to teachers’ autonomy support will be collected (see Supplementary Material Table S1). The lists should be completed periodically to obtain an adequate follow-up of the intervention and, thus, to help teachers to develop some of the more complex strategies. In the Supplementary Material Table S1, a checklist is provided with general items based on the PASSES [19], to encourage students’ autonomy with support from teachers. This checklist will be complemented with items that address the strategies co-created with the PE teachers in the training programme so they can be adjusted to the school’s educational reality.

### 2.3. Measures

The following measures were applied to evaluate the variables at three different times (February, June, and October) in the study participants to determine and identify which students could be part of the intervention programme based on psychosocial and physiological dimensions. To summarise, all the instruments are shown in Table 1.

*Socio-economic Status.* The FAS Scale [46] is an index composed of four items that are indicators of material wealth: How many cars or vans does your family own (0, 1, 2 or more)? Do you have a room to yourself (0, 1)? During the last 12 months, how many times did you go on holiday with your family (0, 1, 2, 3 or more)? How many computers does your family own (0, 1, 2, 3 or more)? The items are scored from 0 to 10. The higher the score, the higher the family’s socioeconomic status. 

*Height and Weight.* Students’ height and weight will be assessed by trained research staff of the same sex as the student. Weight will be measured with a digital electronic scale (model SECA 877), and height will be assessed with a telescopic height-measuring instrument. Both measurements will be taken twice, and the mean value will be used to calculate the body mass index.

*Perceived Need Support in PA.* The Spanish translation of the Perceived Autonomy Support Scale for Exercise Settings [19], adapted by Moreno-Murcia et al. [47], will be used. This scale has 12 items (i.e., “I feel that the PE teacher gives me choices and opportunities about whether to do sport and/or vigorous exercise in my free time”) grouped into a single factor (teacher autonomy support). The response format is a Likert scale ranging from 1 (strongly disagree) to 7 (strongly agree).

*Motivation for Physical Activity.* To assess motivation to practice physical-sports activity, an adaptation of the Behavioural Regulation in Exercise Questionnaire (BREQ-3; [48]), validated for the Spanish context by González-Cutre et al. [49], will be used. This scale begins with stem “I exercise because…”, followed by 23 items, grouped into six factors that measure intrinsic motivation (i.e., “it’s fun and satisfying to exercise”), integrated regulation (i.e., “it is consistent with my lifegoals”), identified regulation (i.e., “I think it’s important to make the effort to exercise regularly”), introjected regulation (i.e., “I feel a failure when I haven’t exercised in a while”), external regulation (i.e., “I feel under pressure from friends/family to exercise”), and amotivation (i.e., “I think exercise is a waste of time”). All the factors have four items except for the identified regulation, which has three. The response format is a Likert scale ranging from 1 (totally disagree) to 5 (totally agree).

*Intention to be Physically Active.* We used the Intention to be Physically Active (MIFA) questionnaire, created by Hein et al. [50] and adapted to the Spanish context by Moreno-Murcia et al. [51]. This instrument was developed with Spanish primary school students [52]. The scale is preceded by the phrase, “Regarding your intention to take up a sporting activity ...”, and comprises 5 items (i.e., “I am interested in developing my physical fitness”). The response format is a Likert scale ranging from 1 (totally disagree) to 5 (totally agree).

*Perception of Physical Activity Levels.* The Spanish-validated scale of Benítez-Porres et al. [53] was used to assess PA in children. This self-administered questionnaire measures moderate to vigorous PA performed in the last seven days in students. It consists of ten items, nine of which are used to calculate the activity level. The other item assesses whether any illness or other event prevented the child from doing their regular activities in the last week. The items are scored from 1 to 5.

*Engagement in Physical Education.* To assess students’ engagement in PE, we will use Skinner et al.’s [54] Student Engagement Questionnaire, adapted by Shen et al. [55]. The scale is preceded by the stem “When I am in PE class…”, and comprises 5 items (i.e., “I work as hard as I can”), which address students’ perceptions of their endeavour, heed, and steadfastness in PE classes. The response format is a Likert scale ranging from 1 (totally disagree) to 5 (totally agree).

*Academic Performance.* Reference to the grades obtained in the 2nd and 3rd trimesters in the subjects of PE, first language (Spanish), mathematics and second language (English). The grade point average (GPA) will then be calculated as an average of the scores in these four subjects. Previous studies have used these subjects as indicators to assess academic performance [56,57].

In addition, to evaluate the process and development of the school-based intervention, semi-structured interviews will be carried out with teachers, students and families in order to obtain complementary information to that obtained from the different questionnaires and scales mentioned above.

**Table 1 children-10-00504-t001:** Summary variables and instruments to measure them used in study.

Variable	Instrument
Socio-economic status	FAS Scale [46]
Height	Stadiometer
Weight	Weighing machine
Perceived Need Support in PA	PASSES [47]
Motivation toward physical activity	BREQ-3 [49]
Intention to be physically active	MIFA [51]
Perception of physical activity levels	PAQ-C [53]
Engagement in physical education	Physical Education Engagement Questionnaire [55]
Academic performance	Grades obtained in 1st and 2nd trimester

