## Abstract

Low levels of physical activity (PA) are a concern among students, producing negative physical, health and mental consequences. This study aims to present a protocol intervention in physical education (PE) based on self-determination theory (SDT) to enhance students’ motivation towards performing PA and increasing their PA levels in their leisure time. This protocol is a convenience study with two allocation arms (intervention group versus control group). SDT-based motivational strategies will be carried out and co-created with PE teachers to increase motivation and out-of-school PA levels. Data collection will be conducted three times: before the intervention, after the intervention (four months after baseline) and at the end of the intervention (retention measurement, seven months after baseline). The measures will assess perceived teacher support for PA, motivation towards PA, intention to be physically active, PA levels, engagement in PE and academic performance. Overall, this intervention programme is expected to increase students’ autonomous motivation for PA and their PA levels in their free time. This intervention might encourage teachers to establish strategies and resources to increase their students’ adaptive outcomes.

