### 1.3. The Present Study

In accordance with the previous studies and the theoretical framework of SDT, we highlighted that: (a) most of the studies were based on different theories; (b) they assessed only variables within PE; (c) they were applied to young people over 12 years of age; (d) PE teachers were not always involved in the intervention; and (e) most of the strategies developed only focused on autonomy support. Therefore, this study aims for the PE teacher to apply a series of SDT-based motivational strategies that support autonomy, competence, and relatedness towards PA in primary education students to improve their motivation for PA and, consequently, their extracurricular PA. For this purpose, an intervention will be carried out in students (10 to 12 years), where strategies will be applied to support the three BPNs (i.e., autonomy, competence, and relatedness) concerning PA and with the teachers playing a more active role, as they will co-create and develop these motivational strategies to promote motivation and out-of-the-school practice of PA.

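### The leisure-time activity aim is assessed by a whole-week activity score that, in June, can include break-time activity delivered by the programme itself

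*Protocol article*

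**What the plan says.** **Aim.** The Abstract speaks of "increasing their PA levels in their leisure time" and describes strategies meant "to increase motivation and out-of-school PA levels". Section 1.3 gives the purpose as "to improve their motivation for PA and, consequently, their extracurricular PA". The Discussion (Section 3) again names leisure-time activity as an expected result.

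**Measure.** Section 2.3 describes one activity instrument (the PAQ-C in Table 1): "This self-administered questionnaire measures moderate to vigorous PA performed in the last seven days in students". On scoring it says: "It consists of ten items, nine of which are used to calculate the activity level". Items run from 1 to 5. No score for time outside school is defined, and no other activity measure is listed. Section 2.4 makes activity a secondary outcome under the neutral label of perceived activity level. The primary outcome is motivation for out-of-school activity.

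**Programme.** Section 2.2 has the strategies developed in the experimental schools, to involve teachers, families and peers "both in the school and in the out-of-school context". One task of the facilitators is "to design a programme of physical-sports activities that include different games and/or sports modalities for break time". Another is to design complementary and extracurricular activities.

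**Timing.** Sections 2.1 and 2.2 place baseline in February, the programme from March to June, the post-test in June and the follow-up in October.

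**The concern.** The aim names a setting, namely time outside school, and the outcome does not. That alone would only add noise if school-time activity were the same in both arms. Here the programme also acts on school time, in the experimental schools and during the period that the June recall can cover.

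The extra school-time activity would be present in one arm and absent at baseline. A group-by-time comparison therefore does not remove it. If the June score is higher in the experimental schools, the plan cannot tell whether children became more active in their own time or were more active in breaks while the programme ran. The first is the effect the study sets out to show. The second says little about whether support from PE teachers carries over into leisure time.

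**Working it through.** The protocol states no figure on this point, so there is none to reproduce. The check is a comparison of texts, followed by an illustration of size.

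**1. Do aim and measure refer to the same activity?** The Abstract and Section 1.3 refer to leisure-time, out-of-school or extracurricular activity. Section 2.3 refers to moderate-to-vigorous activity over seven days, in one nine-item score. The measure is wider than the aim. The protocol does not list the items, so the inclusion of school time is inferred from the unrestricted recall and the single score.

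**2. Does the programme act on the part that should be excluded?** Section 2.2 includes break-time games and sports. The list of facilitator tasks names no arm, but the strategies are developed in the experimental schools and the facilitators serve that programme. It is a fair inference that the control schools do not receive these activities.

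**3. Which measurements are exposed?**

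| Measurement | Position relative to the programme (March to June) | Recall can contain delivered school activity? |
|---|---|---|
| February | before | no |
| June | at its end or as it finishes | yes, experimental schools |
| October | after, next school year | much less; the Discussion says materials stay in the schools |

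**4. How large could it be?** Assumptions, none of them in the protocol:
- the score is the mean of the nine items;
- k items concern school time;
- each of these rises by d points in the experimental schools;
- no other item changes.

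Then the shift in score is k × d / 9.

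| k | d = 0.5 | d = 0.6 | d = 1.0 |
|---|---|---|---|
| 1 | 0.06 | 0.07 | 0.11 |
| 2 | 0.11 | 0.13 | 0.22 |
| 3 | 0.17 | 0.20 | 0.33 |
| 4 | 0.22 | 0.27 | 0.44 |

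For example, 3 × 0.6 / 9 = 0.20.

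**5. Would such a shift count as an effect under the plan?** Assume a standard deviation of 0.6, which is also not in the protocol. The shifts for d = 0.6 and k = 2 to 4 are then 0.133/0.6 = 0.22 to 0.267/0.6 = 0.44 standard deviations. In a simple comparison of two equal groups, eta squared = D²/(D² + 4), with D the standardised difference. This gives 0.049/4.049 = 0.012 to 0.198/4.198 = 0.047. Section 2.4 calls values above 0.01 small and above 0.06 moderate. On these assumptions, a gain confined to school time would be classed as a small effect.

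**The case against.** **Total weekly activity is a legitimate outcome for this programme.** Section 2.1.2, Section 2.2 and the Discussion all say that activity in school is promoted too. This stands. It is a reason to keep the total, but it does not let the total support a leisure-time conclusion.

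**The analysis section does not call the score leisure-time activity.** It uses a neutral label, and activity is secondary. This also stands. A reader might infer that the study is bound to report an in-school gain as a leisure-time gain, but the documents do not support that. The leisure-time reading comes from the aim and the Discussion, so the risk is one of interpretation.

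**The item content is unknown.** A split by setting may or may not be possible. This stands, and any re-scoring must be conditional on it.

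**The in-school component may be slight.** A reader might infer that the experimental schools receive supervised sessions in school hours. The text says only that facilitators design a break-time programme. It gives no supervision, frequency or amount, and it also lists extracurricular activities, which fit the aim. So the protocol does not show that the school-time contribution is large.

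**Scoring detail belongs in an analysis plan that is not shown.** This carries only part of the weight. The article itself fixes the instrument, the nine-item score and the intended conclusion, and these do not match.

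**Conclusion.** The point holds as a mismatch between the leisure-time aim and the only activity outcome. It matters mainly for the June comparison. An arm difference there could come from activity delivered in school, and the planned score cannot show otherwise. October is much less exposed.

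The conclusion rests on two inferences: that an unrestricted seven-day score includes school time, and that the break-time activities reach only the experimental schools. Both follow naturally from Sections 2.2 and 2.3, but neither is stated outright.

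The size is unknown. The range of 0.13 to 0.27 points, for 2 to 4 school-time items each rising by 0.6, is illustrative and is not evidence that a bias of that size will occur. Because activity is secondary and the remedy is cheap, this is a worthwhile improvement and not a flaw in the main comparison.

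**What to change.** In Sections 2.3 and 2.4:

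1. Keep the validated nine-item total as an outcome, and describe it as total weekly physical activity.
2. Check whether the questionnaire items can be separated by setting.
3. If they can, prespecify an additional score from the items on time outside school, and report the school-time items separately. Draw the leisure-time conclusion only from the out-of-school score.
4. If they cannot, limit the conclusion to total weekly activity, and say that the June value may include activity delivered by the programme in school.

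**Cost.** Scoring rules and wording only; the questionnaire is unchanged and no new data are needed. The drawback is that an out-of-school score has fewer items, is less reliable than the total and is not separately validated. This is why it should stand beside the total and not replace it.
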